**Figure 2 F2:**
[figure not shown]
**Time points of assessment.** 1) LSAS self rating, 2) LSAS observer rating.

Independent and trained SCID interviewers giving patient assessments are blind to the treatment condition. Assessments will be made at baseline, that is, prior to treatment onset (T1), at session 8 (T2), 15 (T3), and 25 (usually post-treatment, T4), at post-treatment (when treatment duration is longer than 25 sessions, T5). Every session is planned to have a 50-min duration. Follow-up assessments will take place 6 (T6) and 12 months (T7) after treatment; assessments at weeks 8 and 15 are performed to ensure intent-to-treat analyses. Primary endpoint: assessment after 25 sessions; secondary endpoint: post-treatment. Should treatment end at T4, measures for T5 will also be collected.

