### Objectives and hypotheses

As a study combining the scientific benefits of randomized controlled trials (efficacy studies) and naturalistic studies (effectiveness research), its main objective is the analysis of the effects of additional training for private practitioners. Hence, the following question is investigated: does training in manualized treatment increase the effectiveness of psychotherapy for social phobia in natural settings?

We expect the effects of CBT on social phobia to be enhanced by training experienced therapists and by systematic transfer of innovative manualized treatments into practice. Thus, the specific hypotheses are as follows: (1) treatment effects achieved by private practitioners trained with the manualized procedures (Group 1) will be superior to those achieved by therapists who continue their standard treatment (Group 2); and (2) treatment duration (in terms of number of sessions between treatment onset and finalization) in Group 1 will be shorter.

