### Medical complications

Only psychological conditions according to the International Classification of Diseases F00-F99 (‘Mental and Behavioral Disorders’) will be recorded and classified as adverse events. Any deterioration that results in discontinuation of therapy (including suicidal risk and hospitalization) will be notified immediately by the private practitioner. Changes in psychological disorders will also be notified by the therapist and assessed by the diagnostician after session 25 of treatment, as well as 6 and 12 months post-treatment.

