### Ethical issues

The trial has been approved by the responsible Ethics Committee of the Technische Universitaet Dresden (EK: 183062010) and the Data Safety Monitoring Committee (DSMC). Prior to assessment, patients will be informed about design and procedures, and will be required to give informed consent and may withdraw at any point without any disadvantage. Participating patients will be provided with a treatment consistent with good clinical practice according to the EMEA guidelines (
http://www.emea.eu.int/pdfs/human/ewp/363503en.pdf) for the diagnosis and treatment of SP. Suicidal tendencies will be examined regularly by the private practitioner. Should the need arise, outpatient services will be available and admission to cooperating clinics will also be possible. For further care, patients that cannot be included in the study will either be added to the practitioner’s general waitlist for further diagnosis and treatment or receive information on alternative potential healthcare practitioners upon request.

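### Before session 25 the only named source of adverse events is the unblinded therapist, and the blinded check is not tied to the end of treatment

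*Protocol article*

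**What the plan says.** The Medical complications section of the protocol article defines the scope, source and timing of adverse-event data. Scope is limited: "Only psychological conditions according to the International Classification of Diseases F00-F99" are recorded as adverse events. The source during treatment is the therapist: "Any deterioration that results in discontinuation of therapy (including suicidal risk and hospitalization) will be notified immediately by the private practitioner". For other changes the rule is "Changes in psychological disorders will also be notified by the therapist and assessed by the diagnostician after session 25 of treatment". The only later checks that the section names are the two follow-ups, at 6 and at 12 months. Under Ethical issues, suicidality is also placed with the therapist: "Suicidal tendencies will be examined regularly by the private practitioner".

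The Assessment section describes the blinded side: "Independent and trained SCID interviewers giving patient assessments are blind to the treatment condition". It schedules trial assessments at baseline (T1), sessions 8, 15 and 25 (T2 to T4), the end of treatment if that is later than session 25 (T5), and 6 and 12 months afterwards (T6, T7). On T5 it adds: "Should treatment end at T4, measures for T5 will also be collected".

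The Randomization section makes the therapist the randomised unit and says that patients do not know whether their therapist was trained. Hypothesis 2, under Objectives and hypotheses, is that "treatment duration (in terms of number of sessions between treatment onset and finalization) in Group 1 will be shorter".

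**The concern.** Outcome ratings are protected by independent blinded assessors. Harms during treatment do not have the same named protection. Until session 25 the only reporter that the article names is a person who knows the allocation and belongs wholly to one arm. If training changes how readily a therapist recognises or reports deterioration, therapist-notified events cannot separate that change from a true difference in harm. Randomising therapists does not remove the problem, because the allocation itself could alter reporting.

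The timing adds a second weakness. A check anchored to session 25 depends on how long treatment lasts. It has no stated counterpart for a patient who leaves earlier, and that group includes anyone whose deterioration ended therapy.

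This matters more than usual here. The Discussion section concedes that harm, in the sense of standard care being better, cannot be ruled out, and that one-sided testing allows no test for it. Adverse-event data are therefore an important separate source on that question.

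**Working it through.** The plan gives no adverse-event rate or power figure to reproduce. The check is mainly a reading of the sections against each other, with two small calculations.

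**1. Which blinded safety check each patient has** (Medical complications against Assessment; the maximum of 25 + 5 = 30 sessions is from Interventions)

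| Patient | Blinded check named during or at end of treatment | Next named check |
|---|---|---|
| Stops before session 25 | None | 6 months, if still followed |
| Ends at session 25 | T4, which coincides with T5 | 6 months |
| Continues past session 25 | T4, while still in treatment; none at T5 | 6 months |

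T2 and T3 are scheduled assessments, but the Medical complications section names no adverse-event check at either.

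**2. How many patients could miss the session-25 check through drop-out**

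Inputs: 162 enrolled and 25% drop-out (Sample size calculation); 116 completers (Abstract).
- From the rate: 0.25 × 162 = 40.5, about 40 patients.
- From the completer count: 162 − 116 = 46, which is 28% of 162.

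The Participants section says that the 25% applies over 2 years, so it may include losses during follow-up. About 40 is therefore an upper bound for drop-outs at the planned rate. The article does not say how many leave before session 25.

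**3. What unequal reporting could do** (all inputs assumed; none is in the documents)

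Observed rate = true rate × proportion reported. With equal true rates, the observed ratio between arms is the ratio of the two reporting proportions. Take 0.9 in one arm, and 162 / 2 = 81 patients per arm. Events are shown for the 0.9 arm against the other arm.

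| Reporting in the other arm | Observed ratio | Events, true rate 5% | Events, true rate 10% | Events, true rate 20% |
|---|---|---|---|---|
| 0.8 | 0.8 / 0.9 = 0.89 | 3.6 v 3.2 | 7.3 v 6.5 | 14.6 v 13.0 |
| 0.7 | 0.7 / 0.9 = 0.78 | 3.6 v 2.8 | 7.3 v 5.7 | 14.6 v 11.3 |
| 0.5 | 0.5 / 0.9 = 0.56 | 3.6 v 2.0 | 7.3 v 4.1 | 14.6 v 8.1 |

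For example, 81 × 0.10 × 0.9 = 7.29 and 81 × 0.10 × 0.5 = 4.05. This shows only that differential reporting can create an apparent difference. The ratio simply returns what was assumed, and either arm could be the one that reports less.

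**4. What Hypothesis 2 implies for ascertainment**

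If Group 1 has fewer sessions, fewer Group 1 patients may reach session 25, so they would be checked less during treatment. Equally, more Group 2 patients may run past session 25 and meet the T5 gap. The two effects act on different arms, so the net direction is not determined.

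**The case against.** Several points against this are sound and limit it.

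- **No planned comparison.** The Statistical analysis section lists no between-arm analysis of adverse events, and the Safety aspects section gives patient safety to oversight bodies. A reader might infer that the trial's arm differences in adverse events are confounded with who reports. The article does not support that: the type of reporter is the same in both arms, and blinded checks exist at T4, T6 and T7. What remains is a risk of bias in therapist-notified events, which would affect any later comparison built on them.
- **Other information may exist.** The article is condensed, Figure 2 is not shown, and symptom scales may be collected at T2 and T3. A reader might infer that no sign of deterioration before session 25 can reach the trial except through the therapist. That cannot be established. The article does, however, name a source and a schedule for adverse events, and that schedule contains no blinded source before session 25.
- **T5 is a narrow gap.** T4 usually is the end of treatment. On the 25 + 5 schedule it precedes the end by at most five sessions, so those patients do have a blinded check during treatment. A reader might also infer that the gap falls mainly on control patients, but that treats an untested hypothesis as fact and ignores its opposite effect on reaching session 25.
- **The mechanism is not shown.** The training described covers treatment techniques, not adverse-event reporting, and both groups are offered supervision. Discontinuation and hospitalisation leave less room for discretion than milder changes. Nothing in the article indicates that reporting does differ by arm; the point is that the stated rule would not protect against it if it did.

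**Conclusion.** The concern holds as a weakness in how harms are ascertained. Before session 25 the only named source is an unblinded therapist nested in one arm. Early stoppers have no named blinded check until follow-up, and patients treated past session 25 have none at T5. Because treatment length is expected to differ by arm, the completeness of checking may differ too.

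The size and direction of any bias cannot be derived from the documents. The one bound available is that at most about 40 of 162 patients (25% over 2 years) could miss the session-25 check through drop-out; the completer figures would put that bound at 46. Patients who finish treatment successfully before session 25 are not drop-outs and are not covered by this bound.

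The conclusion assumes that the schedule in the Medical complications section is the operative one and that Figure 2 adds no adverse-event check. It does not touch the primary analysis. The change is worth making because it is cheap and because no stated analysis has to be altered.

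**What to change.** In the Medical complications section:

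1. Tie the diagnostician's safety check to the end of treatment as well as to session 25: at T5 for patients treated longer, and after the last session for those who stop early. Date the 6- and 12-month checks for early stoppers from that last session.
2. Add a short adverse-event question set, identical in both arms, completed by the patient at the existing assessments T2 to T7 and returned to the trial centre rather than through the therapist. Patients are not told their therapist's arm, which makes them a suitable source.
3. State that any comparison of harms between arms rests on these two sources, and that therapist-notified events are reported separately. Leave therapist notification in place for prompt alerts.

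The cost is a wording change and a few minutes per existing assessment. For a patient who stops early, the check after the last session may mean one contact that would otherwise not take place.

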### Ethical issues

The trial has been approved by the responsible Ethics Committee of the Technische Universitaet Dresden (EK: 183062010) and the Data Safety Monitoring Committee (DSMC). Prior to assessment, patients will be informed about design and procedures, and will be required to give informed consent and may withdraw at any point without any disadvantage. Participating patients will be provided with a treatment consistent with good clinical practice according to the EMEA guidelines (
http://www.emea.eu.int/pdfs/human/ewp/363503en.pdf) for the diagnosis and treatment of SP. Suicidal tendencies will be examined regularly by the private practitioner. Should the need arise, outpatient services will be available and admission to cooperating clinics will also be possible. For further care, patients that cannot be included in the study will either be added to the practitioner’s general waitlist for further diagnosis and treatment or receive information on alternative potential healthcare practitioners upon request.

## Discussion

In the last decade, several authors have emphasized the large gap between therapeutic treatments validated at university institutions and the treatments applied in ‘everyday practice’ (for example
[20,48,49]). These researchers argue for an increasingly efficient and effective dissemination of evidence-based treatments in light of empirical data indicating that, while such psychological treatments are being developed for a variety of psychopathological conditions (for an overview for depression see
[50], for anxiety
[51]), their application into routine clinical practice remains impaired. The factors to which the cause of this problem has been attributed to include a lack of knowledge about the effective transmission of CBT skills, the mechanism of action of CBT, and the minimum dose that patients require, in addition to the difficulties in measuring quality of therapy
[52].

As a means to bridge this gap, the present study (SOPHO-PRAX) represents a first attempt to test the transferability of new CBT treatment options to the private clinical practice under controlled conditions. SOPHO-PRAX thus implies a continuation of the multicenter project evaluating the efficacy of cognitive behavioral therapy (CBT) and psychodynamic short-term therapy (STPP) (SOPHO-NET
[21]). The novelty of the present CBT trial lies in the advantage of combining the elements of randomized controlled trials and naturalistic studies. It will directly inform about the incremental effects of procedures established in a controlled clinical trial into practice. Study results may be of great relevance to healthcare policy, health insurance companies, and the statutory boards of psychotherapists. They may serve to improve quality of treatment and shorten the timeframe between the development and widespread use of effective methods, thereby reducing health cost of expenditures
[53]. The design of SOPHO-PRAX thus aims to further a faster and more widespread dissemination of effective treatments. As one study center is located in East Germany, study results will be of specific importance for deliverance of evidence-based psychotherapeutic interventions in this region and its unmet needs for psychotherapy.

The present study will also be the first to include systematic CBT training of private practitioners in the field of psychotherapy in the German healthcare system. It will help clarify whether clinical practitioners will generally regard the new CBT approaches as helpful for their work, and ascertain to what degree they will integrate the new methods into their clinical routine. As we specifically expected the new methods to be superior, it needs to be mentioned that we choose one-sided testing and an alpha of 0.05 as appropriate for a superiority trial
[54]. There are two reasons for this decision. Firstly, in the field under investigation there is clear and robust evidence (not just expectation) that the manualized approach of CBT for social phobia according to Clark and Wells is the most efficacious among other CBT treatments (see
[15]). It follows that the scientific hypothesis to be tested is one-sided. Secondly, as our study approach is that of a transfer or dissemination trial of an already established manualized procedure, only a clear advantage of this procedure over the reference intervention (non-manualized treatment) would have consequences for practice. Given these two conditions (that is, one-sidedness of scientific hypothesis and practice relevancy for superiority of the to-be implemented treatment only), we followed the recommendation of authors, such as Bland and Altmann
[55] or Knottnerus and Bouter
[56], and calculated the *a priori* sample size estimation based on one-sided testing. This approach warrants that the sample size is not larger than needed and the study is economic.

However, the clear methodological disadvantage of this decision has to be emphasized: Although it is not our scientific hypothesis, we can certainly not rule out ‘harm’, which in our case would mean superiority of the (non-manualized) reference treatment over the to-be implemented manualized one. Given the logic of the one-sided analysis, no statistical testing whether the standard procedure is superior to the manualized one can be made. Accordingly, a negative result in a superiority trial (like ours) would not prove that the investigated therapies are equivalent
[54].

Nevertheless, the results of this study will not only inform about the degree to which the new methods lead to an improvement of treatment course and outcome, but also about whether the effects of routine psychotherapeutic treatment are comparable to those of the controlled, strictly manualized treatments of the SOPHO-NET study
[21]. Finally, this study will allow an estimate of the reduction in treatment duration and costs made possible through implementation of treatment manuals into clinical practice. All these questions will be examined in a methodologically rigorous manner, as they seem highly relevant both for the domain of social phobia and the dissemination of psychosocial treatments in general.

### Trial status

Patient recruitment for the present trial is ongoing and expected to be completed by September 2013. Therapies are expected to be completed in 2014.

## Abbreviations

ANOVA: Analysis of variance; ASQ: Affective Style Questionnaire; ADIS-IV: Diagnostic interview; AE: Adverse event; BDI: Beck Depression Inventory; BMBF: Federal Ministry of Education and Research; BSPS: Brief Social Phobia Scale; CBT: Cognitive behavioral therapy; CRF: Case report form; CGI: Clinical Global Impression scale; CSSRI: Client Sociodemographic and Service Receipt Inventory; DMSC: Data Monitoring and Safety Committee; DSM-IV-TR: Diagnostic and Statistical Manual of Mental Disorders 4th edition, text revision; EC: Ethics Committee; EQ-5D: Quality of life questionnaire; ES: Effect size; HAQ: Helping Alliance Questionnaire; ICC: Intracluster correlation coefficient; ICD-10: International Classification of Diseases; ITT: Intention to treat; KKS : Control center for clinical studies; LOCF: Last observation carried forward; LSAS: Liebowitz Social Anxiety Scale; RCT: Randomized clinical trial; SAD: Social Anxiety Disorder; RTQ: Reaction to treatment questionnaire; SAD: Social anxiety disorder; SAE: Serious Adverse Event; SCID: Structured Clinical Interview for DSM Disorders; SOPHO-NET: Social Phobia Psychotherapy Research Network; SOPHO-PRAX: Study on the transfer of manualized CBT for social phobia into clinical practice; SP: Social Phobia; SPAI: Social Phobia and Anxiety Inventory; SPK: Social Cognitions Questionnaire; STPP: Short-Term Psychodynamic Psychotherapy; SPV: Social Behavior Questionnaire; STEPP: Session evaluation sheet; T1-T7: Time points of assessment.
